## Abstract

**Background:**

Conventional vertical sleeve gastrectomy (cVSG), the most commonly performed bariatric surgery, is associated with low complications, durable weight loss, and significant improvement of many obesity-related comorbidities. However, numerous studies have reported that patients who underwent the cVSG have worsening or new onset (*de*
*novo*) gastroesophageal reflux disease (GERD) which could be related to a negative effect of the operative procedure on the geometry of the gastroesophageal junction impacting on the function of the native gastroesophageal valve. It is imperative to innovate the cVSG procedure because chronic GERD is a debilitating condition associated with increased risk for Barrett’s esophagus and esophageal cancer. INNOVATE-VSG aims to test whether a modified flap valve-preserving VSG (*fvp*VSG), compared to cVSG, will be associated with improvement of preexisting GERD.

**Methods:**

The *fvp*VSG incorporates the following surgical modifications that strengthen the antireflux barrier: achieving 3 cm intrabdominal esophageal length; repair of the diaphragmatic crura; and preservation of 3 cm length of gastric fundus/cardia during the sleeve gastrectomy procedure which will be used to symmetrically wrap around the distal esophagus (120–160° wrap) to restore the naturally occurring gastroesophageal valve. A total of 44 obese patients (BMI 35–50 kg/m^2^) with pathologic GERD, confirmed by abnormal acid exposure time (AET), will be randomly assigned to cVSG or *fvp*VSG in this pilot randomized clinical trial at two academic sites. The primary outcome is the change in AET at 6–9 months after surgery. Secondary outcomes include changes in the lower esophageal sphincter pressure, compliance of the esophagogastric junction, weight loss, and quality of life.

**Discussion:**

Data generated from the INNOVATE-VSG trial will be used to design a larger multi-center randomized clinical trial to confirm the value of preserving a functioning gastroesophageal valve following sleeve gastrectomy.

## Introduction

Bariatric surgery is the most effective treatment for obesity with clinically significant long-term weight loss along with amelioration or resolution of obesity-related comorbidities [1–4]. According to the American Society of Metabolic and Bariatric Surgery (ASMBS), approximately 280,000 operations were performed in the USA in 2022 for bariatric surgery [1]. The majority of these operations were the conventional vertical sleeve gastrectomy (cVSG), accounting for 57.4% of all bariatric operations. The Roux-en-Y gastric bypass (RYGB) is the second most common primary bariatric procedure, accounting for 22.2% of cases [5]. The reasons for the greater use of the cVSG include its procedural simplicity, i.e., no need for a gastrointestinal anastomosis, short operative time, ability to be performed as an outpatient procedure, durable long-term weight loss, and significant improvement of many obesity-related comorbidities. However, many studies have reported an unintended consequence of the cVSG which is worsening or new onset (*de*
*novo*) gastroesophageal reflux disease (GERD) following the surgery. Depending upon the method of assessment and the follow-up duration, GERD incidence post-cVSG varied considerably with some studies reporting up to 68% [6–11]. A 2012 International Sleeve Gastrectomy Expert Panel reported an average GERD incidence of 31% after cVSG [9]. A 2020 meta-analysis estimated that 23% of patients developed *de*
*novo* GERD after cVSG. [10] DuPree et al. in an analysis of 4832 patients undergoing cVSG found that 84% continued to have GERD symptoms postoperatively [7]. In the SM-BOSS trial conducted in Switzerland, patients with severe obesity were randomly assigned to cVSG (*n* = 107) or RYGB (*n* = 110) [12]. At 5-year follow-up, *de*
*novo* GERD was reported by 18/57 (32%) and 6/56 (11%) in the cVSG and RYGB groups, respectively. Among the patients who had preoperative GERD, 32% in the cVSG group had worsening of symptoms compared to 6% in the RYGB group. In the SLEEVEPASS trial conducted in Finland, patients with severe obesity were randomized to either cVSG (*n* = 121) or RYGB (*n* = 119) [13]. GERD symptoms worsened at 10-year follow-up among 44/90 (49%) patients who had cVSG and 8/85 (9%) who had RYGB [13]. Using 24-h impedance, pH study, and manometry testing, Poggi et al. found that among VSG patients, the prevalence of pathological reflux increased from 47.2% preoperatively to 88.7% postoperatively; average DeMeester score increased from 16.7 (normal being < 14.7) to 42.9; LES pressure decreased from 12.3 to 8.9 mmHg, and the stimulated gastric pressure increased from 27.1 to 133.0 mmHg. [14] Although RYGB is an appropriate surgical alternative in the management of patients with obesity and preexisting pathologic reflux, this procedure is associated with a higher risk of complications including the risks for anastomotic marginal ulceration, dumping syndrome, bowel obstruction, and internal herniation, thus reducing its attractiveness as a primary bariatric operation [13, 14].

The GERD after cVSG was thought to be primarily related to the high-pressure, non-compliant system and technical issues associated with narrowing of the gastric incisura leading to a partial, distal gastric obstruction following sleeve gastrectomy [9, 15]. However, despite technical improvements in the construction of the sleeve over the years, GERD continues to plague this surgical procedure. We postulated that GERD development after sleeve gastrectomy is not related to individual skill level of the surgeon but rather due to the anatomic disruption of the antireflux barrier (ARB) as it relates with the specific technique of the cVSG operation, as it currently stands.

The cVSG, which reduces the gastric volume, did not consider the importance of avoiding the disruption of the ARB, which can lead to worsening of GERD. One of the native mechanisms protective against reflux is that the esophagus enters on the side of the stomach at an angle which results in the formation of a gastroesophageal valve mechanism. The latter can be seen on the retroflex view of the esophagogastric junction during endoscopic examination. The cVSG resects the entire gastric fundus and essentially creates a continuous tube with the esophagus entering directly into the stomach, thus eliminating the naturally-occurring gastroesophageal valve. Elimination of the gastroesophageal flap valve (GEFV) is one of the most important mechanisms for the increased risk of GERD after cVSG [16]. With the understanding that disruption of the ARB leads to the development of GERD, our trial proposes a surgical modification which is described as a flap valve preserving VSG (*fvp*VSG). The main technical modifications in the proposed *fvp*VSG include surgical principles that strengthen the ARB. Specifically, the technique for *fvp*VSG includes dissection of the esophageal hiatus with increasing the intra-abdominal esophageal length and repair of the diaphragmatic crura, both of which are not commonly performed in the cVSG unless there is a large hiatal hernia (Fig. 1). Additionally, the stapling technique for cVSG is altered, instead of gastric transection line going through the angle of His at the esophagogastric junction; it is performed 3 cm lateral to the angle of His thus preserving a small portion of the fundus/cardia (Figs. 2 and 3). This modification prevents disruption of the gastric sling fibers as shown in Fig. 3. Additionally, the preserved gastric fundus/cardia allows it to be wrapped around the distal esophagus (120–160° fundoplication) between 1 and 5 o' clock position, which we believe recreates the angle of His and preserves the GEFV (Figs. 4 and 5). This newly constructed gastroesophageal complex preserves the gastroesophageal valve that can act as a barrier to reflux. The latter can be visibly seen on endoscopic exam at follow-up (Fig. 6). The technical modifications described above align with the well-known principles of antireflux surgery (i.e., Nissen fundoplication) in the management of pathologic reflux. However, this technical innovation is not considered as a conventional fundoplication procedure combined with a sleeve gastrectomy as the preserved gastric fundus/cardia is too small to effectively perform any standard fundoplication procedures (i.e. Nissen, Rossetti-Nissen, Toupet, Dor, ect.). The goal for this innovation is more to reestablish the naturally-occurring flap valve that acts as an excellent antireflux barrier [16]. The proposed antireflux mechanism of the *fvp*VSG is related to the impact of gastric distention acting upon the esophageal high pressure zone [17]. In summary, the proposed *fvp*VSG is a technical innovation that incorporates the principles of antireflux surgery into cVSG to minimize GERD.

**Fig. 1 Fig1:**
[figure not shown]
Laparoscopic esophageal hiatus dissection to achieve 3 cm intraabdominal esophageal length and closure of the diaphragmatic crus to strengthen the antireflux barrier

**Fig. 2 Fig2:**
[figure not shown]
Gastric resection in the cVSG goes directly through the angle of His which disrupts the gastric sling fibers and eliminates the naturally-occurring gastroesophageal valve, defined as an anatomic valve composed of a segment of gastric fundus in direct apposition to the intraabdominal esophagus. In contrast, the *fvp*VSG strengthens the antireflux barrier by including (1) dissection of the hiatus to achieves 3 cm intraabdominal esophageal length, (2) preserving 3 cm of gastric fundus/cardia, and (3) performing partial wrap (120–160°) around the distal esophagus, thus preserving the gastroesophageal valve. The proposed antireflux mechanism of *fvp*VSG is related to the impact of gastric distention acting upon the esophago-gastric high pressure zone

**Fig. 3 Fig3:**
[figure not shown]
Laparoscopic gastric stapling with preservation of 3 cm gastric fundus/cardia

**Fig. 4 Fig4:**
[figure not shown]
Schematic drawing of the flap valve preserving sleeve gastrectomy

**Fig. 5 Fig5:**
[figure not shown]
Laparoscopic preservation of the gastric fundus/cardia followed by reestablishing the angle of His and 120–160° partial wrap around the distal esophagus. It should be noted that the wrap occurs between 1-5 o'clock position with a goal to reestablish the naturally-occurring gastroesophageal valve

**Fig. 6 Fig6:**
[figure not shown]
Endoscopic view of cVSG versus *fvp*VSG at 6 months follow-up. Endoscopic view of the *fvp*VSG demonstrates a visible gastroesophageal valve, whereas the cVSG shows a wide hiatal opening without a mechanical antireflux barrier to the esophagus

## Methods and Study Research Design

INNOVATE-VSG is a randomized, single-blind, parallel-design clinical trial with a 12-month follow-up, anticipated to enroll patients at two sites. A total of 44 subjects with BMI of 35–50 kg/m^2^, meeting eligibility for bariatric surgery, and having concomitant pathologic GERD (defined as acid exposure time [AET] of ≥ 4.9% as assessed by the Bravo pH study) will be assigned in 1:1 ratio to cVSG or *fvp*VSG. Recruitment is competitive, i.e., one site may recruit more patients than the other. Only the surgeons and the statistician will be unblinded to the randomized treatment assignment; others including the staff performing mechanistic assessments will remain blinded throughout the trial. As is the standard practice at both sites, the patients will have pre- and post-surgery assessments and non-surgical ancillary interventions including diet and lifestyle counseling.

The primary aim is to determine whether *fvp*VSG will be associated with lower acid exposure to the esophagus as assessed by the change in the total AET% at month 6–9 relative to AET% at baseline, as assessed by the Bravo pH study.

To elucidate the mechanistic basis for the primary aim, the following tests will be performed pre-operatively and 6–9 months post-surgery: (1) high-resolution esophageal manometry (HREM) [18] to assess the LES pressure and intragastric pressure; (2) impedance planimetry (EndoFLIP) [19] to assess changes in the gastroesophageal junction compliance; and (3) assess the length of the flap valve via the retroflex view on endoscopic examination at follow-up [18, 19]. Additionally, the resected stomach specimen will be examined for the presence of gastric sling fibers. The impact of change in GERD symptoms on quality of life (QoL) will be examined with two validated rating scales—GERD-HRQL and SF-36 [20, 21]. Body weight and serum metabolic panel (standard testing for bariatric surgery patients) will also be assessed pre-operatively and at 12-month follow-up. All inclusion and exclusion criteria are listed on Table 1.

**Table 1 Tab1:** Study inclusion and exclusion criteria

Inclusion criteria	Exclusion criteria
1. Male and female subjects aged 18–60 years 2. BMI 35–50 kg/m^2^ 3. Must meet the BMI criteria before and after 6 months of nonsurgical weight management 4. Presence of abnormal acid exposure time (AET) of 4.9% or above as assessed with the Bravo pH test 5. Have health insurance which pays for the costs of bariatric surgery and standard medical care before and after surgery 6. Women of childbearing potential must be using appropriate contraception to avoid pregnancy throughout the study 7. Must be able to provide written informed consent	1. Hiatal hernia > 2 cm 2. Evidence of significant major esophageal motility disorder 3. Severe gastroparesis 4. Previous bariatric or anti-reflux procedure 5. Barrett’s esophagus 6. Subjects requiring mesh treatment at time of procedure 7. Severe heart/lung disease (e.g., heart failure, unstable coronary artery disease, end-stage lung disease) 8. Subjects with pacemakers, implantable defibrillators, neurostimulators 9. Portal hypertension or cirrhosis 10. Chronic pancreatitis 11. Active cancer treatment 12. Inability to tolerate general anesthesia 13. Uncontrollable coagulopathy 14. Significant and uncontrolled inflammatory bowel disease 15. Severe and/or uncontrolled psychiatric disorder 16. Suicidal ideation or unstable/untreated major depressive disorder within the past year 17. Alcohol or substance use disorder within the past year 18. Pregnant, breastfeeding or plan pregnancy in the coming 24 months 19. Diminished intellectual capacity to consent or follow pre- and post-surgery instructions 20. History of, or any current health condition that would make the subject ineligible for sleeve gastrectomy, or put the subject at risk by participation in the study

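### Assessor blinding throughout the trial cannot hold for whoever performs or reads the postoperative retroflex flap-valve assessment

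*Protocol article*

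**What the plan says.** Under Methods and Study Research Design the trial is introduced as follows: "INNOVATE-VSG is a randomized, single-blind, parallel-design clinical trial with a 12-month follow-up". The same paragraph then says who knows the allocation: "Only the surgeons and the statistician will be unblinded to the randomized treatment assignment", and "others including the staff performing mechanistic assessments will remain blinded throughout the trial". The second statement has no exceptions, either by test or by time point.

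The same section lists three mechanistic tests: high-resolution manometry (HREM), EndoFLIP, and a third that is to "assess the length of the flap valve via the retroflex view on endoscopic examination at follow-up". Study Objectives repeats flap-valve length on the retroflex view as a secondary endpoint.

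On what that view shows, the Introduction says that cVSG removes the native valve. Of the valve preserved by fvpVSG it says: "The latter can be visibly seen on endoscopic exam at follow-up". The Fig. 6 legend, comparing the two operations at 6 months, says that the fvpVSG view "demonstrates a visible gastroesophageal valve, whereas the cVSG shows a wide hiatal opening without a mechanical antireflux barrier to the esophagus".

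**The concern.** The blinding sentence is a claim about the design that will be carried into the trial report. It covers every person who makes a mechanistic assessment. By the article's own description, one of those assessments means looking directly at the anatomy that one operation preserves and the other removes. Someone who can see the arm cannot be blinded to it.

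Two things are at stake. First, valve length is a human reading of an image. If the reader knows the arm, the between-arm difference in length lacks the protection that the article claims for it. Second, the article says the data will be used to design a larger multi-center trial. Mechanistic results presented as blinded, when one of them was not, would be given more weight there than they deserve.

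**Working it through.** No arithmetic bears on this point. It does not depend on the sample size, error rates or effect size, and the article gives no figure to reproduce. The check sets the statements side by side.

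1. **Who is said to be blinded.** Everyone except the surgeons and the statistician, with mechanistic-assessment staff named explicitly, for the whole trial (Methods and Study Research Design).
2. **Whether the retroflex examination is a mechanistic assessment.** Yes. It is item 3 in the numbered list of mechanistic tests in the same section: "assess the length of the flap valve via the retroflex view on endoscopic examination". Its reader therefore falls under the blinding sentence.
3. **Whether it counts as an outcome.** Yes. Study Objectives lists it among seven secondary endpoints: LES pressure, junction compliance, flap-valve length, quality of life, GerdQ symptoms, percent weight loss and PPI use.
4. **What the reader sees.** After fvpVSG, a visible valve. After cVSG, a wide opening with no mechanical barrier (Fig. 6 legend). The Introduction agrees on both sides: the fvpVSG valve is visible at follow-up endoscopy, and cVSG eliminates the valve.
5. **Whether the timing matches.** Fig. 6 shows the 6-month view. The postoperative mechanistic tests are planned for 6–9 months, so the figure describes the window in which the endpoint is read.

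Steps 1 and 2 put this assessor among the blinded staff. Steps 4 and 5 say that the assessment itself generally reveals the operation. The two cannot both be true for that person.

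The limits of the inference were checked in the same way:

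- **Preoperative tests.** No operation has been done, so nothing is revealed.
- **HREM, EndoFLIP and Bravo.** The article does not say whether the staff for these tests also perform or see the retroflex view, or in what order the tests are done. With separate staff, blinding can hold. With shared staff and the retroflex view done first, it cannot.
- **Primary endpoint.** Change in total AET% comes from a pH recording device. Nothing in the article shows that knowledge of the arm enters that reading.
- **Patient-reported outcomes.** These depend on patient blinding, which this point does not question.

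**The case against.** The strongest reply is that seeing the arm is intrinsic to this measure. Valve length describes the structure that the operation preserves or removes, no procedure can mask it, and the proposed change mainly relabels it. The Statistical Analysis section names HREM and EndoFLIP as the secondary analyses and reaches valve length only through its general closing sentence. Fig. 6 is also illustrative and does not prove that every patient's view gives the arm away.

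Most of this stands, and it keeps the point small. It does not rescue the sentence. That the measure cannot be masked is exactly why the article should not say that its assessor stays blinded. The single-blind label does not help either, because the sentence goes beyond the patient and names the assessment staff. A fuller protocol might add procedures, but the published statement would still be wrong for this assessor.

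A reader might infer three stronger conclusions that the documents do not support:

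- **That the unblinded statistician also breaches the stated blinding.** The article declares the statistician as an exception, so what it states is what is delivered. Rules for the analysis sets and any masking of labels belong in a statistical analysis plan that is not shown, and their absence here is not a finding.
- **That EndoFLIP, HREM and Bravo readings are unblinded too.** This needs shared staff or a particular test order, and the article gives neither.
- **That the primary result is biased.** The endpoint is device-recorded, and no route from the endoscopic view to the AET value is described.

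**Conclusion.** The point holds in a narrow form. The assurance that mechanistic-assessment staff remain blinded throughout is wrong as written for whoever performs or reads the postoperative retroflex view. In extent, it touches one of three mechanistic tests and one of seven secondary endpoints, after surgery only. The share of examinations that reveal the arm, and the size of any resulting bias, cannot be derived from the article.

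The conclusion rests on one assumption: that the endoscopic appearances in the Introduction and Fig. 6 are typical of trial patients at 6–9 months. The article presents them that way. Any effect on LES pressure or junction compliance is conditional on shared staff. The statistician's access to allocation is declared and forms no part of this conclusion. It is worth correcting because the claim is a stated property of the design that the trial will not have. It does not undermine the primary comparison.

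**What to change.** 1. Amend the blinding sentence in Methods and Study Research Design so that it excepts the person who performs or reads the postoperative retroflex examination.
2. Report flap-valve length as an unblinded, descriptive measure of the surgical anatomy.
3. To keep the claim true for the other tests, record HREM and EndoFLIP before the retroflex view wherever the same staff are involved.
4. Read AET, LES pressure and compliance from coded files that carry no endoscopic images or operative details.

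The cost is a change of wording, some file coding, and a slightly less favourable blinding claim. No extra patients or tests are required. Whether another reader is needed depends on staffing at the two sites, which the article does not give. If the endoscopist also reads EndoFLIP, a separate reader of the coded files may be necessary. Coded reading does not remove bias that enters while a recording is being made, which is why the recording order in step 3 matters. The article describes the trial as not yet open, so the change can be made before any postoperative assessment takes place.

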### Study Objectives

*Primary endpoint*
Change in the total AET% at 6–9 months, relative to pre-surgery AET%, as assessed with the Bravo pH test.

*Secondary endpoints:*
Changes in LES pressure, assessed by HREMChanges in gastroesophageal junction compliance, assessed by EndoFLIPAssess the length of the flap valve via the retroflex view on endoscopic examinationChanges in health-related quality of life as assessed with GERD-HRQL and the SF-36 questionnairesChanges in GERD symptoms assessed with the GerdQ questionnairePercent total bodyweight loss at month 12Proton pump inhibitor (PPI) use

*Safety study endpoints:*
Adverse and serious adverse events30-day and 12-month complications

### Statistical Analysis

Primary and secondary analyses will be performed using an intent-to-treat (ITT) protocol (i.e., all randomized subjects). Additional sensitivity analyses using modified ITT protocols will be implemented with adjustment for missing data. Per-Protocol analysis will also be conducted to test intervention effect under optimal conditions. The primary efficacy outcome (also used for power analysis) is the change in AET% at month 6–9 relative to AET% at baseline which will be analyzed using an analysis of covariance (ANCOVA) model with fixed effects for treatment group, age, sex, race, baseline weight, and baseline AET%. Secondary analyses will include (1) HREM measures and (2) EndoFLIP measures. Additional analyses will include, but are not limited to, GerdQ score, proportions of subjects with GERD improvement or remission, proportions of subjects with *de*
*novo* GERD, proportions of subjects with worsening of GERD based on symptom score, proportions of subjects with shifts in AET% categories, DeMeester score, quality of life measures (GERD-HRQL, SF-36), and percent weight loss. Dichotomous outcomes will be analyzed using a generalized linear model (GLM), specifically, a log-binomial regression model with fixed effects for treatment, strata, and covariates described above. For each between-treatment group comparison of interest, the estimated risk ratio (relative risk), standard error, 95% Wald confidence interval, and *p*-value will be presented. Logistic regression models will also be explored to generate odds ratios to allow for comparability to existing literature regarding efficacy of pharmacologic interventions. The weight loss measure as a continuous variable will be analyzed using linear mixed models (LMM). All secondary and exploratory outcomes will be analyzed using similar models described above (ANCOVA, GLM, and LMM) under the ITT, modified ITT, and per-protocol procedures.

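### The primary ANCOVA omits the strata term that the same section puts in the model for dichotomous outcomes; the cost is nil to modest and the mismatch is easily removed

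*Protocol article*

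**What the plan says.** All the model statements are in the Statistical Analysis section of the protocol article.

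- **Primary endpoint (change in AET% at month 6–9):** an "analysis of covariance (ANCOVA) model with fixed effects for treatment group, age, sex, race, baseline weight, and baseline AET"%. This is a complete list of six terms, with no strata term and no site term.
- **Dichotomous outcomes:** "a log-binomial regression model with fixed effects for treatment, strata, and covariates described above". The covariates referred to are those of the ANCOVA. Strata are named separately, beside them.
- **Other secondary and exploratory outcomes:** models similar to these, so the continuous ones inherit the ANCOVA list.

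On design, the Methods and Study Research Design section says that the trial is "anticipated to enroll patients at two sites", that the 44 patients "will be assigned in 1:1 ratio to cVSG or" the modified procedure, and that "Recruitment is competitive, i.e., one site may recruit more patients than the other". The article does not say that randomisation is stratified and does not say what the strata are.

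**The concern.** The two models, stated a few sentences apart, do not agree. As written, shifts in AET% category would be adjusted for strata, while the continuous change in the same AET% measurement, which is the primary endpoint, would not. One of two things must be true. Either randomisation is stratified and the primary model drops the strata, or it is not stratified and the strata term in the binary model refers to nothing.

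The first case has a statistical consequence. Stratified allocation balances the arms on the stratum, so the treatment estimate is already protected from variation between strata. If the analysis model omits the stratum, that variation stays in the residual. The model-based standard error then exceeds the true sampling variability, the test rejects too seldom under the null, and power is lost. In a trial of 44 patients it is worth knowing how large that loss could be.

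**Working it through.** **1. The plan's own figure.** The article says that "The primary efficacy outcome (also used for power analysis) is the change in AET% at month 6–9 relative to AET% at baseline", but it gives no alpha, power, effect size or SD, so 44 cannot be reproduced. For scale only, assume a two-sided alpha of 0.05 and 22 patients per arm. The detectable standardised difference is d = (z₀.₉₇₅ + z_power) × √(2/22).

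- 80% power: (1.960 + 0.842) × 0.3015 = 0.845
- 90% power: (1.960 + 1.282) × 0.3015 = 0.977

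An effect of 0.9, between the two, is used below.

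**2. What to expect.** Let the omitted factor explain a share R² of the variance that remains after the listed covariates. With balanced (stratified) allocation, the ratio of the standard error without the factor to that with it is about 1/√(1 − R²):

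- R² = 2%: 1/√0.98 = 1.010
- R² = 5%: 1/√0.95 = 1.026
- R² = 10%: 1/√0.90 = 1.054
- R² = 20%: 1/√0.80 = 1.118

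**3. Simulation.** From the documents: N = 44, 1:1 allocation, two sites, and an ANCOVA with treatment and five covariates. Assumed: one two-level factor; each covariate, including race, taking one degree of freedom; the R² values; site splits of 50:50 and 70:30; effect 0.9 in units of the residual SD. Residual degrees of freedom are 44 − 7 = 37 without the factor and 36 with it. There were 10,000 runs per setting, so the Monte Carlo standard error is about √(0.05 × 0.95/10,000) = 0.2 points for type I error and √(0.78 × 0.22/10,000) = 0.4 points for power.

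Stratified randomisation, 50:50 split:

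| R² of factor | SE ratio, without/with | Power without | Power with | Type I error without | Type I error with |
|---|---|---|---|---|---|
| 0% | 0.997 | 78.0% | 77.7% | 5.3% | 5.2% |
| 2% | 1.009 | 78.2% | 78.5% | 4.7% | 4.8% |
| 5% | 1.022 | 77.8% | 79.0% | 4.5% | 5.0% |
| 10% | 1.056 | 78.4% | 81.5% | 4.0% | 4.9% |
| 20% | 1.122 | 79.5% | 86.2% | 3.1% | 5.3% |

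The standard-error ratios agree with step 2. A 70:30 split gives nearly the same picture: ratios of 1.026, 1.053 and 1.118 at 5%, 10% and 20%, with power losses of 80.1 − 78.5 = 1.6, 81.7 − 78.7 = 3.0 and 85.7 − 79.8 = 5.9 points.

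**4. If randomisation is not stratified.** Type I error without the factor stays at 4.8% to 5.2% in every setting, so the test is valid. The choice then concerns precision only. At R² = 0, adding the factor costs slightly over a point of power (77.6% without, 76.4% with, 50:50 split). At 20% it gains about 7 points (77.9% without, 85.2% with).

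**The case against.** The strongest reply is that the documents establish a mismatch of wording and little more. Several parts of that reply stand.

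- **Site.** A reader might infer that the plan adjusts its binary model for site. It does not say so: it says only strata, undefined. Two sites, competitive recruitment and a technique-dependent operation make site a reasonable candidate, no more.
- **Overlap.** The strata might be sex, or categories of baseline AET% or weight. The ANCOVA already contains sex, baseline AET% and baseline weight, so little or nothing would then be left out.
- **Size.** A reader might infer that the omission certainly inflates the standard error and loses power. That requires stratified randomisation, a factor not already covered, and a factor that still predicts AET change after adjustment for baseline AET%. The documents establish none of these, and no R² value above comes from them.
- **Direction.** The error is on the safe side. In the stratified case the point estimate is essentially as precise as before; what suffers is the calibration of its standard error, and hence power. In the unstratified case, chance imbalance between sites is already allowed for in the test.
- **Setting.** This is a pilot meant to inform a larger trial, and an article normally leaves randomisation details and mixed-model terms to the full protocol or SAP. Their absence here is no fault.

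What the reply does not remove is the contradiction itself. The article does not leave the primary model open: it lists every term, and then uses a different set for the binary outcomes.

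**Conclusion.** The inconsistency is certain; its cost is conditional. If the strata are randomisation factors not already represented in the ANCOVA, the primary standard error is overstated by about 0–1% when they explain up to 2% of residual variance, 2–3% at 5%, 5–6% at 10% and 12% at 20%. The matching power losses are about 0–1, 1, 3 and 7 points, and type I error falls to about 4% at 10% and 3% at 20%. These figures rest on N = 44, a standardised effect of 0.9, a single two-level factor and assumed R² values.

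A reader might go further and see a threat to the validity of the primary result. The documents do not support that: under neither kind of randomisation does the omission cause bias or too many false positives. This is a consistency correction worth making, with a possible gain in power.

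**What to change.** State the randomisation strata once and use the same set in every model:

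- **If randomisation is stratified:** add the strata as fixed effects to the primary ANCOVA and the continuous secondary models, and keep them in the log-binomial model. Include site if it is a stratification factor. A stratum already represented by a listed covariate needs only a sentence saying so.
- **If it is not stratified:** delete strata from the log-binomial model, and prespecify whether site is a covariate.

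The decision should be fixed before outcome data accrue, since the article says that the statistician is not blinded to assignment.

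The cost is one sentence in the protocol and SAP and about one degree of freedom per added term. In the stratified 50:50 simulation, a factor with no prognostic value changed power from 78.0% to 77.7%, which is within simulation error.
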